##### Multimorbidity Illness Perceptions Scale

The Multimorbidity Illness Perceptions Scale (MULTIPleS)^40^ was developed to measure patient illness perceptions in the presence of MM. The MULTIPleS is a 22-item questionnaire. Each item has a Likert scale that runs from 0 to 3, where ‘0’ indicates that a person ‘strongly disagrees’ with an item and ‘3’ indicates that a person ‘strongly agrees’ with an item. Overall, the 22 items comprise five subscales: emotional representation, treatment burden, prioritising conditions, causal links and activity limitations. The MULTIPleS is a relatively new scale, so it has not yet been used as a measure in clinical research. However, Gibbons *et al*^40^ found that the scale provided a good fit to the Rasch model and demonstrated evidence of reliability and validity for each of the subscales.

### Economic evaluation

The economic evaluation will be based on a number of questions relating to usage of healthcare services and financial costs to the participant (similar to Raftery, Ryan & Normand^41^). More specifically, we will examine costs that fall on the health and social care services by recording hospitalisations (frequency and duration), outpatient appointments, accident and emergency appointments, types and amounts of benefits received per month, community services used (eg, general practitioner and home help), and medication type, dosage and frequency. These services/products will be translated into unit cost data for Ireland and provide an estimate of the cost of MM where CP is a feature for the health service. Furthermore, we will calculate indirect costs incurred personally by each individual with MM and their family. These will include expenditure for treatments and medications not paid for by the state, and the travel and wait time costs associated with availing of health services. Opportunity costs will also be calculated by quantifying work absenteeism or reduced employment due to MM. To generate these data, information on wages will be collected; however, should collection of this information not be possible, we will extrapolate income from age, education and work type.

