### Aims of the current research

To determine the prevalence, impact and cost of MM in a cohort of people in Ireland who live with chronic pain.To identify the nature and profile of MM in which chronic pain is a central feature.To develop a predictive model of multimorbid disability in a population of people with chronic pain.To chart the developmental trajectory of MM in a sample of people with chronic pain.

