#### Sample size

Sample size was calculated using the equation proposed for prevalence research by Naing *et al*.^18^ To calculate the sample size for a prevalence study, the expected prevalence is required. Based on previous research,^6^
^7^
^14^
^19^ the expected prevalence of MM in a population of people with CP is approximately between 22% and 54%. Nicholl^20^ notes that if there is a doubt about the prevalence total in a given population, researchers should err towards assuming a 50% prevalence rate as it will yield a larger sample size. Therefore, using Naing *et al*'s^18^ equation and predicting that 50% of our sample may exhibit MM, CIs set at 0.95 and the degree of precision (d)=0.05 produced a sample size of 384. Using a predicted response rate of 40%, based on previous Irish prevalence research in the area of chronic pain, the sample size was calculated as 960. Since we are sampling from Irish pain clinics, the design effect of using a cluster randomised trial must be taken into account; however, we were unable to identify a suitable intracluster correlation coefficient. Therefore, as demonstrated in a similar study on prevalence,^14^ a median value of 0.01 was used. Adjusting for this, with an average of 150 patients per cluster, gives a design effect of 2.49 and a sample of 2391. A target sample of 2400 will be recruited, 150 patients from each of the 16 Irish pain clinics.

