### Statistical analyses

Graphical (eg, box plots, labelled scatter plots and case profile plots) and numerical summaries (means, medians, SDs and IQRs) will be provided for all variables. A χ^2^ test will be used to evaluate the relationship between gender and number of conditions. ORs will be calculated for risk factors of MM. Factors associated with MM will be analysed using univariate multiple regression and hierarchical regression will be employed to examine the relationships among the number and type of conditions and the outcome variables (ie, depression, anxiety, quality of life, illness perceptions and severity of pain, for example). All analyses will be conducted using SPSS V.22.

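### The cost of multimorbidity is planned without a contrast to chronic pain alone, and welfare benefits are listed as a health-service cost

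*Protocol article*

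**What the plan says.** The first aim is: "To determine the prevalence, impact and cost of MM in a cohort of people in Ireland who live with chronic pain". The Economic evaluation section of the protocol article sets out three components.

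- **Health-service cost.** Hospital, outpatient, emergency and community service use and medication are recorded and converted with Irish unit costs. The result is to "provide an estimate of the cost of MM where CP is a feature for the health service". The list of items falling on health and social care services also includes "types and amounts of benefits received per month".
- **Personal cost.** The text reads: "we will calculate indirect costs incurred personally by each individual with MM and their family".
- **Lost work.** The text reads: "Opportunity costs will also be calculated by quantifying work absenteeism or reduced employment due to MM".

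The section states no comparison with participants who have chronic pain without multimorbidity (MM), and no rule for dividing cost between pain and other conditions. The Statistical analyses section relates the number and type of conditions to outcomes given as "depression, anxiety, quality of life, illness perceptions and severity of pain, for example". Cost is not named there, but the list is open.

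Under Inclusion criteria and Recruitment, every participant has chronic non-cancer pain and is sampled from patients seen at a pain clinic in the preceding 18 months.

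**The concern.** Pain-clinic visits and pain medication would appear in these people's costs even if they had no other condition. A total built from all their recorded use therefore contains the cost of the pain itself. Calling that total the cost of MM invites the reader to take it as what MM adds.

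The wording does not settle which quantity is meant. The health-service item can be read as a total for people with both. The lost-work item is phrased as an attributable cost, with no means given of separating MM from pain. The personal-cost item is restricted to people with MM, so on that wording no difference could be formed for it. Two quantities thus share one name.

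Cost is one of the three quantities in the first aim, and the Abstract motivates the study by the extra use and expense that further conditions bring. A gross total cannot answer that.

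Benefits raise a second issue. They are transfer payments, not a service with a unit cost, and they partly replace earnings that the same section values as lost work.

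**Working it through.** **1. The plan's own figures.** The article states no cost figure. Its only arithmetic is the sample size: "CIs set at 0.95 and the degree of precision (d)=0.05 produced a sample size of 384", at an assumed prevalence of 50%.

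- Precision: 1.96² × 0.5 × 0.5 / 0.05² = 384.1 (stated 384).
- Response of 40%: 384 / 0.40 = 960 (stated 960).
- Design effect: 1 + (150 − 1) × 0.01 = 2.49 (stated 2.49).
- Target: 960 × 2.49 = 2390.4 (stated 2391, rounded up).

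These reproduce. They bear on the cost question only by showing whether an internal comparison group is expected.

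**2. Gross total against increment.** Let A be the mean cost with chronic pain alone, B the mean cost with chronic pain and MM, and R = B / A. Then gross total / increment = B / (B − A) = R / (R − 1). R is not in the documents, so the values below are assumptions.

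| Assumed R | Gross total / increment |
|---|---|
| 1.25 | 5.0 |
| 1.5 | 3.0 |
| 2 | 2.0 |
| 3 | 1.5 |
| 5 | 1.25 |

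The ratio exceeds 1 whenever pain alone costs anything and MM adds cost. It is largest where MM adds least.

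**3. Benefits and lost work.** Let b be benefits as a share of lost earnings (assumed; not in the documents). If the two were added, the sum divided by lost earnings would be 1 + b: 1.2, 1.4, 1.6 and 1.8 for b = 0.2, 0.4, 0.6 and 0.8. This applies only if they are added.

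**4. Is a contrast feasible?** The Sample size section gives an expected range of 22% to 54% and plans on 50%. The target of 2400 at 40% response gives 2400 × 0.40 = 960 responders. The table also shows the unadjusted requirement of 384.

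| Prevalence of MM | Of 384: with / without | Of 960: with / without |
|---|---|---|
| 22% | 84 / 300 | 211 / 749 |
| 50% | 192 / 192 | 480 / 480 |
| 54% | 207 / 177 | 518 / 442 |

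On the plan's own expectations both groups are substantial. The Recruitment section sends the same survey pack to everyone selected, so no separate recruitment is needed.

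**The case against.** The strongest reply is that the planned figure answers the question as worded. The article defines MM as coexisting conditions with none primary. Chronic pain is then one of the conditions making up the MM, and its cost belongs in the total. Subtracting it treats pain as the index disease. This stands in part: the total cost of people with both is a legitimate descriptive quantity and should be kept. It does not explain why lost work is worded as attributable, and it does not let the total show what further conditions add.

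A second reply is that this is a condensed article, and that attribution rules and cost models belong in a fuller plan. That is fair for the choice of model. It is less persuasive for what the article already fixes: which items are costed, for whom personal costs are calculated, and under what name the result is reported.

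Three stronger readings are tempting, and the documents do not support them.

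- **That benefits are added to lost work.** The article lists benefits with service costs and lost work separately as an opportunity cost. It mentions no combined total.
- **That the cost will be substantially overstated.** No cost figure in the documents supports any size, and whether the recorded use is all-cause is not stated.
- **That cost is excluded from the regression analyses.** The outcome list is given as examples, so cost may be included.

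**Conclusion.** The point holds as a matter of what is being estimated and how it is labelled. As written, the plan cannot show what MM adds to chronic pain. If the health-service total is read as cost attributable to MM, it is too high by an amount the documents do not allow to be computed. That direction rests on two premises: chronic pain alone carries cost in a pain-clinic population, and recorded use is not limited to the other conditions. The ratios of 1.25 to 5.0 show only how the result depends on an unknown input.

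Placing benefits among health and social care service costs is a misclassification whatever is summed later. The double count is a conditional risk, not a stated plan.

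The change should be made, because cost is part of the first aim and the data needed are already to be collected.

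**What to change.** - Cost every respondent, including personal costs and lost work, whether or not they have MM.
- Label the gross figure as the total cost of people with chronic pain and MM, and keep it as a descriptive result.
- Add the adjusted mean cost difference between respondents with and without MM, or the cost per additional non-pain condition. Use a model suited to skewed costs, such as a gamma model with log link, adjusted for age and sex and accounting for clinic. The per-condition version is the safer choice if fewer respondents than expected turn out to be without MM.
- Adjust for pain grade only as a sensitivity analysis. The grade includes disability, which MM may itself affect, so adjusting could remove part of the cost of interest.
- Report benefits separately as transfers, outside the health-service cost, and never sum them with lost earnings.
- Name cost among the outcomes in the Statistical analyses section.

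This costs wording and analysis time, with no new variables. The small downside is that the incremental figure will be lower and less precise than the gross total.

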### Statistical analyses

Graphical (eg, box plots, labelled scatter plots and case profile plots) and numerical summaries (means, medians, SDs and IQRs) will be provided for all variables. A χ^2^ test will be used to evaluate the relationship between gender and number of conditions. ORs will be calculated for risk factors of MM. Factors associated with MM will be analysed using univariate multiple regression and hierarchical regression will be employed to examine the relationships among the number and type of conditions and the outcome variables (ie, depression, anxiety, quality of life, illness perceptions and severity of pain, for example). All analyses will be conducted using SPSS V.22.

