## Introduction

The guidelines for chronic disease management have traditionally taken a single disease approach,^1^ which presents a challenge for patients who have multiple, sometimes discordant chronic conditions. As such, it has been argued that a single-morbidity approach in the context of multiple health conditions typically leads to inadequate disease management.^1^ Thus, there has been a call for a more ‘holistic’ consideration of the patient and a disease management approach that focuses on multimorbidity.^1^
^2^ Multimorbidity (MM) refers to the coexistence of two or more chronic conditions within one person, where no one condition takes precedence over another.^3^ Despite the increasing interest of healthcare practitioners in the area of MM, Marengoni *et al*^4^ note that there remains “a remarkable gap between the harmful impact of multimorbidity at the individual and societal level and the amount of scientific and clinical research devoted to this topic” (p.435).

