##### Process for developing the current MM checklist

In line with Fortin *et al*'s^26^ recommendations, the conditions included in the current disease count questionnaire were obtained from two large-scale national reports on the Irish population more widely^25^
^26^ and four Irish research studies that had investigated the prevalence of MM and had compiled lists of conditions to examine.^6^
^19^
^26^
^27^ To ensure that the list of conditions met international best practice recommendations,^21^
^23^ in terms of which conditions to include in an MM disease count list, we then combined our study with one international study that examined MM in people living with CP.^5^ We also examined two of the most recent systematic reviews, which outline the most common conditions included in MM studies and contain recommendations for the type of conditions to be included in MM checklists.^10^
^28^ Following this, two healthcare practitioners were consulted and provided feedback on which conditions to include, and one clinician, who is an expert in chronic pain, reviewed the entire MM checklist. From this review process, the three additional categories of conditions included were as follows: renal disorders, hepatic disorders and headache disorders. Subsequently, we collapsed the conditions from this developmental process with respect to the CIRS organ system domains and removed any duplicate conditions, leaving us a total of 34 conditions across 10 organ domains (see table 1). We also added category options (eg, ‘Other cardiac conditions’) to ensure that useful data could be collected on conditions that did not appear on the list, as well as a final ‘Any other condition not listed’ category.

**Table 1 BMJOPEN2016012131TB1:** Source and summary of conditions included in the Multimorbidity Checklist

CIRS domain	Study and included conditions									Included MM Checklist conditions
	Teljeur *et al*^27^	Naughton *et al*^6^	Household Quarterly Report 2010	CARDI 2011/Savva *et al* 2011 unpublished manuscript	TILDA 2011 Report: Fifty plus in Ireland	Diederichs *et al*^10^ (systematic review)	Sinnige *et al*^28^(systematic review)	Agborsangaya *et al*^5^	Sinnott *et al*^19^	

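### The chi-square test of gender against number of conditions ignores the order of the count and so loses power; an ordered or count model would serve better, and the model behind the ORs should be named

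*Protocol article*

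**What the plan says.** In the Statistical analyses section of the protocol article, a chi-square "test will be used to evaluate the relationship between gender and number of conditions". No grouping of the count is given, and no trend version of the test. Two further statements follow: "ORs will be calculated for risk factors of MM" and "Factors associated with MM will be analysed using univariate multiple regression". Logistic, ordinal and count models are not named.

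The count comes from the checklist described under the process for developing it, "leaving us a total of 34 conditions across 10 organ domains", with further options for conditions not listed. MM itself "refers to the coexistence of two or more chronic conditions within one person" (Introduction), so it is a yes/no classification derived from a count. Age and gender are both collected (Sociodemographic and health information).

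**The concern.** Number of conditions runs 0, 1, 2, 3 and upward, and the order carries the information. If women tend to have somewhat more conditions than men, the difference appears as a shift along that scale. A Pearson chi-square test does not look for a shift. It spreads its sensitivity over every possible departure from equal distributions, using one degree of freedom for each category beyond the first. A rank test, a trend test or a count model concentrates on the shift. The two-way test also has no place for age or clinic.

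At stake is a gender difference that the data could show but the chosen test may miss. A smaller matter is that the article does not make clear which regression will produce the ORs for MM.

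**Working it through.** **The plan's own figures.** The sample size rests on prevalence precision: "predicting that 50% of our sample may exhibit MM", with "CIs set at 0.95 and the degree of precision (d)=0.05 produced a sample size of 384".

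- n = z²p(1−p)/d² = 1.96² × 0.5 × 0.5 / 0.05² = 384.16, stated as 384.
- Response of 40%: 384 / 0.40 = 960.
- Design effect: 1 + (150 − 1) × 0.01 = 2.49.
- 960 × 2.49 = 2390.4, stated as 2391; target 16 × 150 = 2400.
- Expected responders: 2400 × 0.40 = 960.

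These reproduce. None concerns the gender comparison, for which no power or effect size is stated.

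**Cost of ignoring order.** Take a shift that a 1-df trend test detects with 80% power at two-sided 5%. The noncentrality is (1.960 + 0.842)² ≈ 7.85. If the trend score captures the whole difference, the unordered test has the same noncentrality on more degrees of freedom:

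| df | 1 | 2 | 3 | 4 | 5 | 10 | 15 |
|---|---|---|---|---|---|---|---|
| power | 0.80 | 0.71 | 0.65 | 0.60 | 0.56 | 0.43 | 0.36 |

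**Simulation against a rank test.** Assumptions not in the documents: 600 women and 360 men, negative-binomial counts with dispersion k = 5, no clustering by clinic.

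| Setting (mean, women vs men) | Chi-square, ungrouped | Six groups (0, 1, 2, 3, 4, 5+) | Three groups (0–2, 3–5, 6+) | Rank test |
|---|---|---|---|---|
| 4.0 vs 3.5 | 0.30 | 0.50 | 0.64 | 0.80 |
| 4.4 vs 3.7 | 0.52 | 0.76 | 0.88 | 0.97 |

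These means imply that about 79% to 86% of people have two or more conditions, well above the 50% used for planning. Under the same model, 50% corresponds to a mean count near 1.8. Two settings at about that level gave 0.26 ungrouped against 0.61 for the rank test, and 0.67 against 0.96. Means of 1.9 vs 1.65 and 2.0 vs 1.6 reproduce these to within about 0.03. The lowest grouped power, about 0.40, comes from the smaller of these two shifts.

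Relative to the rank test, the loss at 4.0 vs 3.5 is 1 − 0.30/0.80 = 62% ungrouped, 1 − 0.50/0.80 = 38% with six groups and 1 − 0.64/0.80 = 20% with three. At 4.4 vs 3.7 it is 46%, 22% and 9%.

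**Other distributions, against a linear trend test.** Assumptions: 960 responders, 60% women, no clustering.

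| Count model | Mean in men | Ratio women/men | Ungrouped | Six groups | Trend |
|---|---|---|---|---|---|
| Poisson | 2 | 1.15 | 0.51 | 0.65 | 0.87 |
| Poisson | 4 | 1.10 | 0.39 | 0.52 | 0.84 |
| Negative binomial, k = 3 | 2 | 1.15 | 0.20 | 0.36 | 0.64 |
| Negative binomial, k = 3 | 4 | 1.15 | 0.21 | 0.44 | 0.80 |
| Poisson | 2 | 1.30 | 0.99 | 1.00 | 1.00 |

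**Sparse cells.** Ungrouped, about 31% of cells have an expected count below 5 in the k = 5 settings, and 23% to 44% across the other settings tried (384 or 960 responders). With the six- or three-group versions of the first table, essentially none do. With no true difference, the ungrouped test rejected in about 3% to 5% of runs, so the problem is lost sensitivity and not false positives.

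**The case against.** The strongest reply is that the article does not say the count is ungrouped. Cut-points are a detail that a fuller plan may hold, and sensible grouping removes the sparse cells and much of the loss. That stands for the sparse cells. For power it stands only in part, because every grouped version with more than two categories still fell short of the ordered comparison unless the difference was large.

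Four stronger readings are tempting, and the documents do not support them.

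- *Most of the power is discarded.* The size depends on a distribution, gender split and effect that the article does not give. At 4.4 vs 3.7 less than half is lost even ungrouped, and for a large shift almost none (0.99 vs 1.00).
- *A linear model is fixed for a yes/no outcome.* The sentence promising ORs comes immediately before the regression sentence and points to a logistic model. The phrase about univariate multiple regression can mean one outcome with several predictors. The model is loosely named, not wrongly chosen.
- *ORs will exaggerate risk-factor effects.* Prevalences of 60% and 40% do give a ratio of 1.5 and an OR of (0.6/0.4)/(0.4/0.6) = 2.25, but the article nowhere reads ORs as risk ratios. ORs are a valid measure.
- *A gender difference would be confounded by age without remedy.* Age is collected and can enter the planned multiple regression. It is only the two-way comparison itself that cannot adjust.

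It is also fair to say that gender appears in none of the four stated aims.

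**Conclusion.** The point holds as a modest improvement to a secondary analysis. The article names a test that does not use the order of the count, and this costs power whenever more than two count categories are kept. With 960 responders and the k = 5 assumptions, power is roughly 0.26 to 0.67 ungrouped and 0.40 to 0.88 grouped, against 0.61 to 0.97 for a rank test. More overdispersed counts gave lower values (0.20 ungrouped, 0.36 with six groups, against 0.64 for a trend test). All these figures rest on assumed means, dispersion and gender split and ignore clustering by clinic. They compare tests and do not forecast this study's power.

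The naming of the regression for MM is a matter of clarity only. The prevalence estimate, which is the main focus, and the sample size are untouched.

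**What to change.** In the Statistical analyses section, replace the chi-square test with a negative-binomial or ordinal regression of number of conditions on gender, adjusted for age and accounting for clinic. If a simple unadjusted comparison is wanted beside it, use a rank or trend test.

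As a clarification, state that the ORs for MM yes/no come from a multivariable logistic regression, in place of the present phrase about univariate multiple regression.

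The cost is a few words. The data are those already planned, the methods are available in standard software, and no additional participants are needed.
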